## Limitations

This study contains several important limitations. First, the patients included in this study may represent a non-generalisable sample of the entire preoperative population. This study includes just one academic medical centre, and its patient population and rules for preoperative assessment clinic attendance may differ from that of other hospitals. In addition, only 65% of eligible preoperative assessment clinic attendees enrolled in the study, which may introduce bias. However, our analyses indicate that participants do not differ in important ways from non-participants. Furthermore, even if the sample was maximally biased, enrolling 65% of the actual target population means the results contain at least 80% accuracy.^28^ Another factor that biases the sample is non-response to the follow-up surveys. Although we mitigated non-response through an extensive follow-up protocol, only 55% of patients complete a 30-day survey.

The surveys also introduce several limitations. While the surveys are entitled ‘30-day’ and ‘1-year’ surveys, and most surveys occur near these times, the dates actually range from 20 to 120 and 275 to 455 days following surgery, respectively. In addition, each survey has two versions. Most questions are similar (readmissions) or identical (functional dependence, quality of life, complications) and can be combined. However, the postoperative falls question is significantly different. We will exclude results from the non-validated version, reducing the sample size available for this question. All important confounders will still be included, but the model may not have a sufficient number of outcomes to test all of the interactions of interest. Since many published papers do not test interactions, we do not think this compromises the robustness of the model.

The variables themselves also contain limitations. While the three explanatory variables and many of the outcome variables come from standardised tools, complications, readmission and fall-related injuries do not (see table 1). For complications and readmission, no gold standard currently exists. Thus, using patient-reported complications and readmission could be a weakness, or it could be a strength. Many variables (Charlson Index, neurological impairment, chronic pain, depression, anxiety) come from the CPAP history and physical or the CPAP physician review of systems, where the degree of completeness is unknown. To address this issue, the informaticist performs careful validation with cross-checks of patient records to ensure accuracy. For the procedural cardiac risk variable, patients do not always undergo the scored procedure. Finally, although the surveys, surgeon note, CPAP records and electronic medical record provide a large quantity of data, not all desired confounders identified through literature search are available. The confounders listed in this protocol are the ones that are available from our database.

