**Ethics and dissemination:**

The home institution's Institutional Review Board approved this study (IRB ID number 201505035). The authors will publish the findings, regardless of the results.

Strengths and limitations of this studyPublishing protocols for observational studies is not routine practice, so this protocol sets a rigorous precedent for similar studies.This is the first trial to describe postoperative falls and the association between preoperative falls and postoperative falls, poor quality of life and functional dependence.The study population is both large (∼8000 patients) and non-selected.The enrolment rate of eligible patients is 65%, baseline survey response is 92% and 30-day survey response is 55%. Non-participation at any of these stages may introduce bias.Variables were not always available or derived from a validated tool.

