## Study groups

The target population for this study is patients who underwent preoperative assessment for elective surgery at Barnes Jewish Hospital in St. Louis, Missouri between 16 January 2014 and 7 October 2015. Over 70% of patients undergoing elective surgery are assessed by the centre for preoperative assessment and planning (CPAP) clinic before surgery. Reasons for no assessment include urgent surgery, geographical limitations or surgeon preference. Inclusion criteria include age 18 or older, ability to read the English consent form, ability to consent and plans to undergo elective surgery. During the analysis phase, patients are excluded from participation in SATISFY-SOS if they have undergone surgery within 60 days of their planned surgery date.

Approximately 65% of all eligible patients consent to participate in the study. Reasons for non-participation include patient refusal (∼70% of cases), lack of nurse time or training (∼20%), or lack of English literacy (∼10%). A study comparing participants to non-participants showed no major differences in characteristics.^19^ Approximately 92% of all consented patients complete a baseline survey. Reasons for lack of complete participation include insufficient time or changing their mind. Overall, the estimated number of eligible patients per YEAR is 15 500, the estimated number of consenting patients per year is 10 000, and the estimated number of baseline survey records per year is 9200. Approximately 16 000 baseline survey records are available in the time period specified for this study (16 January 2014 to 7 October 2015).

For the purposes of this substudy, only the first complete record for each patient (ie, baseline survey and corresponding 30-day survey) will be included in the final data set (∼94% of the available records). This practice ensures that each record is statistically independent from all the other records.

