## Data

### Data to be collected

Incomplete follow-up is a major source of bias in many long-term observational cohort studies. To maximise completeness of 30-day and 1-year follow-up data, the following sequence of contact methods is performed. First, the survey is emailed up to three times starting ∼20 days after the surgery date. For those who did not provide an email or who do not respond to the emails, a paper survey is also mailed 25 days after the surgery date. If a patient does not respond to the first paper survey, a second paper survey is mailed 21 days later. If the second paper survey is not returned, the patient is phoned up to five times. Using this aggressive protocol, the 30-day survey response rate between 16 January 2014 and 7 May 2015 was ∼55%. An identical process occurs for the 1-year survey, beginning 365 days after the surgery date. For the date ranges included in this study, two versions of the 30-day survey (V.2 and V.3) and two versions of the 1-year survey (V.1 and V.2) were administered to participants. See online supplementary material to view these surveys.

10.1136/bmjopen-2016-011570.supp4Supplementary data

10.1136/bmjopen-2016-011570.supp5Supplementary data

10.1136/bmjopen-2016-011570.supp6Supplementary data

10.1136/bmjopen-2016-011570.supp7Supplementary data

Access to the SATISFY-SOS data is limited to investigators and staff who: have access to the Department of Anesthesiology desktop computers, have a computer account with the Department of Anesthesiology, use an IP address from within the department offices, have written permission to analyse the data from the principal investigator, and have authorised access to the database. For this project, the investigators formulated a list of requested data. They will provide that list to the informaticist, who manages the SATISFY-SOS database and has access to other medical records data. Using queries in MetaVision (iMDsoft, Needham, Massachusetts, USA), the informaticist will provide the requested survey and medical record data to the investigators. The query start date will be 16 January 2014 since important survey revisions occurred before this date.

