### Analysis

To begin analysis, we will perform descriptive statistics of all variables used in the analysis, using means, SDs and Student's t-tests for normal, continuous variables; medians, IQRs and Mann-Whitney tests for non-parametric, continuous variables; and proportions and χ^2^ tests for categorical variables. We will explore and report differences between patients with follow-up surveys at 30-days compared with non-responders.^26^ Among patients included in the analysis, we will also explore and report differences between those with complete records versus those with missing data. For variables with missing data, we will perform multiple imputation where appropriate.

Our first aim is to describe the characteristics of postoperative falls in an unselected surgical population, such as their occurrence, timing, injuries and risk factors. To achieve that goal, we plan to perform the following analyses:
Descriptive statistics:
Per cent who fell while still in the hospital;Number of falls (0, 1, 2, 3+) and fall rate in the 30 days and 1-year following surgery;Fall rate and per cent who fell by surgery type (10 surgery departments);Injuries from falls in the 30 days following surgery;Injuries from falls in the 1 year following surgery.▸χ^2^:
Proportion with any injury, comparing preoperative falls to postoperative falls at 30 days and 1 year;Proportion with severe injury, comparing preoperative falls to postoperative falls at 30 days and 1 year.Risk factors: see results from logistic regression model in Aims 2a–c.

As a subaim of Aim 1, we also plan to explore the rate of falls in the short-term versus long-term postoperative periods. To accomplish this, we will calculate the rate of falls per 100 person-years in the Behavioral Risk Factor Surveillance System (BRFSS) system, which serves as the control rate of falling in the general population of adults in the USA. We will then convert the 30-day, 6-month and 1-year fall rates from the SATISFY-SOS population into falls/(100 person-years) using the BRFSS distribution. Finally, we will compare the observed rate of falling to the general population's rate of falling at 1 month and 1 year (Student's t-test) to estimate how the rate of falls changes after surgery.

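### The assurance of at least 80% accuracy counts only the 65% enrolment stage, whereas the 30-day results come from about 33% of eligible patients

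*Protocol article*

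**What the plan says.** The Limitations section first accepts that enrolling 65% of clinic attendees may introduce bias. It then says that, even under maximal bias, "enrolling 65% of the actual target population means the results contain at least 80% accuracy", citing a reference. The sentences that follow name survey non-response as a further source of bias and report that "only 55% of patients complete a 30-day survey". The 80% figure is left as it stands.

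The three stages are stated elsewhere:

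- Study groups: "Approximately 65% of all eligible patients consent to participate in the study".
- Study groups: "Approximately 92% of all consented patients complete a baseline survey".
- Data to be collected: "the 30-day survey response rate between 16 January 2014 and 7 May 2015 was ∼55" per cent.

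The strengths and limitations list after the abstract gives all three rates together and adds: "Non-participation at any of these stages may introduce bias".

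Study groups also states that the final data set holds only the first complete record per patient, meaning a baseline survey with its matching 30-day survey. On non-response, the Analysis section says: "We will explore and report differences between patients with follow-up surveys at 30-days compared with non-responders". It then turns to missing data among patients included in the analysis and plans multiple imputation where appropriate.

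**The concern.** An assurance that results stay at least 80% accurate under maximal bias has to count every stage at which patients can drop out of the results. This one counts the first of three. A patient who consents but returns no 30-day survey contributes nothing to any reported outcome, just like a patient who refused consent.

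The protocol itself calls incomplete follow-up a major source of bias in long-term cohort studies. The results most exposed are the descriptive fall rates of Aim 1, because a rate among responders equals the population rate only if non-responders fall equally often. A reader who takes the 80% figure at face value would trust those rates more than the design allows.

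**Working it through.** **Inputs.** Enrolment 65% and baseline completion 92% (Study groups); 30-day response about 55% (Data to be collected); 15 500 eligible patients per year and about 16 000 baseline records from 16 January 2014 to 7 October 2015 (Study groups); over 9000 records with both surveys and a 30-day fall proportion of about 10% (Sample size calculations).

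**Step 1: coverage from the stated rates.** 0.65 × 0.92 = 0.598 have a baseline survey. 0.598 × 0.55 = 0.329 have both surveys. If the 55% refers to all consented patients instead, coverage is 0.65 × 0.55 = 0.358.

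**Step 2: coverage from the counts.** The window is 1.72 years, so eligible patients number about 15 500 × 1.722 ≈ 26 700. Baseline records: 16 000 / 26 700 = 59.9%, matching 59.8% in step 1. Complete records: 9000 / 26 700 = 33.7%, matching 32.9%. The two routes agree.

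**Step 3: the plan's 80%.** The article gives no formula and the cited source is not shown, so the figure cannot be reproduced. As an assumption, take worst-case bounds for a proportion. With coverage f and observed proportion p, the full-population value lies between f·p and f·p + (1 − f). Reporting the midpoint gives a largest error of (1 − f)/2 whatever p is, which is the best case.

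| Patients counted | f | Largest error (1 − f)/2 | Best-case accuracy |
|---|---|---|---|
| Enrolled | 0.650 | 0.175 | 82.5% |
| Enrolled, baseline survey | 0.598 | 0.201 | 79.9% |
| Enrolled, baseline and 30-day survey | 0.329 | 0.336 | 66.4% |

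On this reading 80% is compatible with 65% enrolment. It is just missed once baseline completion is counted, and missed by a wide margin once 30-day response is counted. For p = 0.10 the bounds widen from 6.5%–41.5% at f = 0.65 to 3.3%–70.4% at f = 0.329.

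**Step 4: what a plausible difference would do to a fall rate.** No document figure shows how response varies with falling, so this is an illustration. If responders fall at 10% and non-responders at 15%, the rate among all surveyed patients is 0.55 × 0.10 + 0.45 × 0.15 = 12.25%. The responder rate is then too low by 1 − 10/12.25 = 18%.

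**Step 5: what weighting can and cannot do for the OR.** Selection multiplies the crude OR by (s11 × s00)/(s10 × s01), where s is the response probability by fall history and postoperative fall. If response depends on fall history alone, the terms cancel and the factor is 1. It departs from 1 only when response depends on the outcome jointly with fall history. For example (assumed), response of 57% with neither kind of fall, 52% with one and 40% with both gives 0.40 × 0.57 / (0.52 × 0.52) = 0.84. Weights built from baseline variables do not in general remove that factor.

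**The case against.** The best defence is disclosure. The 80% sentence is attached to enrolment, the next sentences name non-response as another source of bias, and all three rates appear in the strengths and limitations list. A careful reader can multiply them. That stands as far as it goes: the protocol does not hide its follow-up. But the sentence makes its promise about the results, and those come only from patients who passed all three stages.

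A second defence is that the Analysis section plans a responder comparison and multiple imputation, and that weighting could sit in an analysis plan that is not shown. In part this stands. The lack of weighting is not an error in the article, and the text does not rule out wider imputation. However, the comparison describes and does not correct. The imputation sentence follows one about patients already in the analysis, so it most naturally covers missing items rather than absent surveys.

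Three stronger readings are tempting and are not supported:

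- That 80% is wrong even at 65% enrolment. This depends on what accuracy means. Distance from the interval midpoint gives 82.5%; distance from an observed 10% gives 1 − (0.415 − 0.10) = 68.5%. Without the cited source neither reading can be called the intended one.
- That participation is only 29%, from 7800 / 26 700. The 7800 also excludes about 600 repeat records and about 600 with unsuitable intervals, so it is not a participation figure.
- That the primary OR is shown to be biased and that weighting would repair it. The 0.84 rests on assumed response rates. If response depends only on covariates already in a correctly specified model, the adjusted OR is not biased by it.

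**Conclusion.** The point holds for the 80% statement. It takes account of enrolment only, while the 30-day results rest on about 33% of eligible patients (33% to 36%, depending on the denominator of the 55%). This follows from the article's own rates and is confirmed by its counts. That the assurance does not carry over to the results needs no assumption about how the 80% was derived. The size of the loss, from 82.5% to about 66% in the best case, does rest on the assumed worst-case bounds.

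The point about the analysis is more modest. The stated plan describes non-response without correcting for it, and a correction for measured baseline factors is possible with data already held. It would help the Aim 1 fall rates most. It would not settle whether the ORs are affected by response that depends on postoperative falls. A reader might infer from the low coverage that the associations in Aim 2 are unreliable, but nothing in the document shows how response relates to falls.

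**What to change.** 1. In Limitations, delete the 80% sentence or confine it in words to the enrolment stage. State that about 33% of eligible patients have both a baseline and a 30-day survey (0.65 × 0.92 × 0.55).
2. Add a sensitivity analysis that reports fall rates at 30 days and 1 year weighted by the inverse probability of response, beside the unweighted rates. Fit the response model on baseline variables such as fall history, age, sex, ASA status, Charlson index, baseline quality of life and function, and surgery type.
3. Fit that model only among baseline-survey patients who were sent the version used for the outcome: V.3 at 30 days and V.2 at 1 year. The Sample size section restricts the fall outcomes to these versions, so a model in all baseline patients would count people sent another version as non-responders.
4. Weighted ORs may be shown as secondary, with a statement that weights from baseline variables do not correct response that depends on the postoperative outcome. A simple missing-not-at-random range, such as step 4 of the working repeated over several assumed non-responder fall rates, would address that for the rates. The same can be done for the OR by varying the response probabilities in step 5.

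The cost is one edited sentence, identification of who was sent which version, and weighted re-runs on existing data. Confidence intervals will be wider, and only measured baseline factors are corrected.

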**Methods and analysis:**

To achieve these goals, we study adult patients who underwent elective surgery at our academic medical centre and were recruited to participate in a prospective, survey-based cohort study called Systematic Assessment and Targeted Improvement of Services Following Yearlong Surgical Outcomes Surveys (SATISFY-SOS) (NCT02032030). Patients who reported falling in the 6 months prior to surgery will be considered ‘exposed.’ The primary outcome of interest is postoperative falls within 30 days of surgery. Secondary outcomes include postoperative functional dependence, quality of life (both physical and mental), in-hospital complications and readmission. Regression models will permit controlling for important confounders.

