	Days from BL to 30 days survey	Continuous	BL survey, Press Ganey	BL completion date to 30 days process date	NA
	Days from BL to 1 year survey	Continuous	BL survey, Press Ganey	BL completion date to 1 year process date	NA
	Surgery type	10 categories	Medical record	BL	NA
	In-hospital falls	Dichotomous	Survey (V.3 only)	30 days	Yes^21^
	In-hospital heart problem or stroke	Dichotomous	Survey	30 days	No
	In-hospital lung complication	Dichotomous	Survey	30 days	No
	In-hospital blood clot	Dichotomous	Survey	30 days	No
	In-hospital kidney or intestine complication	Dichotomous	Survey	30 days	No
	In-hospital nerve injury	Dichotomous	Survey	30 days	No
	In-hospital infection	Dichotomous	Survey	30 days	No
	In-hospital delirium	Dichotomous	Survey	30 days	No
	Other in-hospital complication	Dichotomous	Survey	30 days	No

ASA, American Society of Anesthesiology; BL, baseline; CPAP, centre for preoperative assessment and planning; H&P, history and physical; METs, metabolic equivalents; NA, not applicable; ROS, review of systems.

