## Statistical considerations

### Sample size calculations

The required sample size is calculated based on the primary outcome, which is a fall within 30 days of surgery. Appropriate logistic regression models contain at least 10 ‘events’ per predictor variable.^20^ Since our prespecified model for postoperative falls includes 13 dependent variables (see the Analysis section), a sample with at least 130 events is required. In our population, preliminary work shows that ∼10% of patients report falling in the month following surgery. Thus, the minimum sample size needed for this study is 1300 patients.

Currently, our database contains over 9000 complete records (ie, baseline and 30-day survey) after the 16 January 2014 start date. To meet statistical assumptions of independent observations, we estimate that ∼600 records from patients with at least one previous entry in the data set will be excluded. We estimate that an additional 600 records will be excluded due to inappropriate time intervals (baseline survey to surgery <0 or >59 days; surgery to 30-day survey <20 or >120 days; or surgery to 1-year survey <275 or >455 days). Thus, our final sample size will be ∼7800.

Within this final sample, two versions of the 30-day (V.2 and V.3) and 1-year surveys (V.1 and V.2) were administered. Only V.3 of the 30-day survey and V.2 of the 1-year survey contain a validated falls question, as recommended by the Prevention of Falls Network Europe consensus group.^21^ The difference in question phrasing caused statistically significant differences in the percentage of patients reporting postoperative falls (5.5% vs 10% at 30 days and 18% vs 28% at 1-year, p<0.001). Out of the available records, about 20% (1500) completed V.3 of the 30-day survey, which is more than the 1300 required for the primary outcome. Thus, to maximise outcome validity, only these versions will be used for postoperative falls. In contrast, the readmission question contained only minor differences (‘Were you readmitted to the hospital?’ for V.2 vs ‘Check all that apply […] admitted to a hospital’ for V.3). The percentage reporting readmission was similar between surveys (5.2% vs 5.7%, p=0.416), so the results from both versions will be combined. The remaining outcomes were identical and will use all available data from both versions of the 30-day and 1-year surveys.

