Presence or absence of at least one fall in the 30 days (primary outcome) and 1 year following surgery:
Physical activity level (<4 vs >4 metabolic equivalents (METs));Baseline altered elimination (bowel or bladder);Baseline mobility abnormality;Dizziness/vertigo;Depression.▸Barthel Index that is worse than baseline, at 30 days and 1 year after surgery:
Baseline Barthel Index score;Neurological impairment;Mood disorder (depression or anxiety);Smoking status.▸Physical quality of life score, at 30 days and 1 year after surgery:
Baseline physical quality of life score;Preoperative physical activity level (<4 vs >4 METs);Chronic pain;Mood disorder (depression or anxiety);Smoking status.▸Mental quality of life score, at 30 days and 1 year after surgery:
Baseline mental quality of life score;Chronic pain;Mood disorder (depression or anxiety).▸Presence or absence of any complication that occurred in the hospital, as reported in the 30-day survey:
Smoking status.▸Presence or absence of readmission at 30 days, as reported in the 30-day survey:
In-hospital complications (30-day survey);Incontinence.

After running each model, we will substitute the number of falls (0, 1, 2, 3+) explanatory variable for the falls and fall injuries composite scale^27^ to evaluate which scale better predicts outcomes. Since we test multiple hypotheses, the threshold for significance will be α=0.01. We will report results using ORs and 99% CIs, along with variance estimates for regression parameters.

Using SAS/STAT software, V.9.4 (SAS Institute, Cary, North Carolina, USA), [name] will perform all analyses. Analysis will begin only after acceptance of this protocol for publication. This approach reassures readers that key analyses were truly prespecified rather than post hoc. If the authors decide to perform post hoc analyses, these will be described as such and will be performed for the purpose of further hypothesis generation.

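### The primary 30-day fall outcome is read from surveys completed 20 to 120 days after surgery, and no planned analysis takes account of the elapsed time

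*Protocol article*

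**What the plan says.** The outcome is fixed at 30 days throughout. The abstract states: "The primary outcome of interest is postoperative falls within 30 days of surgery". The Sample size calculations section states: "The required sample size is calculated based on the primary outcome, which is a fall within 30 days of surgery". The Analysis section models "Presence or absence of at least one fall in the 30 days (primary outcome) and 1 year following surgery".

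The measurement is wider. Sample size calculations excludes only records with "surgery to 30-day survey <20 or >120 days", so any survey from day 20 to day 120 counts. The contact schedule in Data to be collected produces this spread: "the survey is emailed up to three times starting ∼20 days after the surgery date", a paper survey at day 25, a second 21 days later (about day 46), then up to five telephone calls.

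The fall model is a logistic regression with forced entry of eight common and five outcome-specific variables. Time from surgery to survey is not among them. Table 1 lists "Days from BL to 30 days survey" as a descriptive variable, but it counts from the baseline survey, which may precede surgery by up to 59 days.

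Limitations discloses the range for the 30-day and 1-year surveys, "the dates actually range from 20 to 120 and 275 to 455 days following surgery, respectively", and adds a mitigating clause, "and most surveys occur near these times". It gives no distribution of response times and no analytic remedy.

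**The concern.** A binary outcome defined over a fixed period needs every patient observed for that period, or an analysis that allows for the difference. Here neither is arranged.

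First contacts go out at about day 20 and day 25, so some patients can answer before day 30. They are scored as having completed the window. At the other end, the problem depends on the item's wording:

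- If it asks about the time since surgery, a late answer includes falls after day 30.
- If it asks about the preceding month, a late answer describes a different month.
- If it asks about the first 30 days, a late answer covers the right period but with longer recall.

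Two results are at stake. The first is descriptive. Aim 1 hypothesises that the fall rate declines from 30 days to 1 year, and the plan converts falls to a rate per 100 person-years. If falls since surgery were divided by a nominal 30 days, the early rate would be inflated in the direction of that hypothesis. The second is the odds ratio for preoperative falls, which could be biased if prior fallers answer at different times from others.

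Thirty-day readmission shares the problem. The version 2 item, as the article quotes it, shows no 30-day limit, and the version 3 item is quoted with an omission.

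**Working it through.** **Inputs from the protocol article**

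- Accepted interval: 20 to 120 days (Sample size calculations; Limitations).
- Fall proportions with the validated item: 10% at 30 days, 28% at 1 year (Sample size calculations).
- Model size: 13 variables, 10 events per variable, about 1500 usable records (Sample size calculations).
- Minimum important difference: 20% in proportions or odds ratios (Sample size calculations).

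**The plan's own figures**

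- Variables: 8 common + 5 specific = 13, with no elapsed-time term.
- Events: 13 × 10 = 130, and 130 / 0.10 = 1300 patients, as stated.
- Power: 1500 patients, 26% exposed, 10% overall risk (8.69% against 13.73%) and two-sided alpha 0.05 give 79.2% for a 58% increase. This agrees with the stated 80%. The calculation treats every patient as having the same 30-day risk period.

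**Width of the window**

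- If the item is tied to the first 30 days, observed windows run from 20 to 30 days: 30/20 = 1.5-fold.
- If the item asks about the time since surgery: 120/20 = 6-fold in time, at the extremes.

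**Fall risk by response day, if the item asks about the time since surgery**

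Assumption: one constant hazard to day 30 and a lower constant hazard afterwards, fitted to 10% at day 30 and 28% cumulative at day 365.

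- h1 = −ln(0.90)/30 = 0.003512 per day.
- h2 = [−ln(0.72) + ln(0.90)]/335 = 0.000666 per day.
- F(d) = 1 − exp{−[h1·min(d,30) + h2·max(0,d−30)]}.

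| Response day | Fitted hazard | Constant hazard h1 throughout |
|---|---|---|
| 20 | 6.8% | 6.8% |
| 30 | 10.0% | 10.0% |
| 46 | 11.0% | 14.9% |
| 60 | 11.8% | 19.0% |
| 120 | 15.2% | 34.4% |
| 365 | 28.0% | 72% |

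The fitted hazard gives a 15.2/6.8 = 2.2-fold spread. The constant hazard passes the protocol's 1-year figure of 28% before day 120, so it is not a usable basis for the size of the effect.

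**Person-year rate**

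Take one fall per faller and, as an assumption, a response at day 45.

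- Dividing by a nominal 30 days instead of the actual 45 overstates the rate over the observed period by 45/30 = 1.5, whatever the proportion. For 10%: 0.10/(30/365.25) = 122 against 0.10/(45/365.25) = 81 per 100 person-years.
- The comparison with the true first-30-day rate is milder. Under the fitted hazard 10.9% have fallen by day 45, and 0.1089/(30/365.25) = 133, against 122 for the first 30 days: about 9% too high.

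**Odds ratio with no true effect**

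Assumption: prior fallers answer later than others, who answer at day 35. F(35) = 10.30%, F(42) = 10.72%, F(45) = 10.89%.

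- Day 42 against day 35: (0.1072/0.8928)/(0.1030/0.8970) = 1.045.
- Day 45 against day 35: (0.1089/0.8911)/(0.1030/0.8970) = 1.065.

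Both are well below the 20% minimum important difference.

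**The case against.** The strongest reply has four parts.

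1. **The item wording is not visible.** A reader might infer that risk windows differ sixfold. That holds only if the question asks about the time since surgery. If it asks about the first 30 days, which is how the Analysis section words the outcome, late responders have a complete window and only answers on days 20 to 29 are truncated. This part stands: sixfold is a conditional maximum.
2. **Large bias in the odds ratio is not supported.** A constant hazard would give null odds ratios of 1.22 (day 42 against 35) and 1.31 (day 45 against 35), above the 20% threshold. That hazard implies 34% at day 120 and 72% at 1 year, against the protocol's 28%. Nor do the documents report that prior fallers answer later. This part also stands.
3. **The range is bounded, disclosed and said to be mostly near the nominal date.** This is fair as to the extremes, but the article gives no distribution, and disclosure does not change the analysis.
4. **Detail may sit elsewhere.** The article does not say that rates are divided by a nominal 30 days, and exact denominators are often left to a fuller plan. So the inflation of the rate is conditional. The covariate list is different: it is given as complete and prespecified, and any later analysis will be labelled post hoc.

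One could add that confounders were restricted to those known at surgery planning, which the survey date is not. But elapsed time would enter as length of observation, not as a preoperative predictor, so that restriction does not bear on it.

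**Conclusion.** The mismatch between the outcome's definition and its measurement is established by the text. Responders on days 20 to 29 have an incomplete window under any wording; at day 20, modelled risk is 6.8% instead of 10%. No planned analysis allows for this or for late response.

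The further size is conditional. If the item asks about the time since surgery, modelled risk within the one nominal 30-day outcome runs from 6.8% to 15.2%. This assumes that the two reported proportions are cumulative from surgery and apply at days 30 and 365. The main exposure is the 30-day proportion and the person-year comparison with 1 year, which would be inflated if a nominal 30 days were used as denominator.

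Bias in the primary odds ratio is possible but not shown. On the protocol's own figures, a 7- to 10-day difference in response time would give a null odds ratio of about 1.05 to 1.07. The point merits correction before analysis begins, as an outcome-definition and denominator problem; it is not evidence that the association would be spurious.

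**What to change.** 1. State the recall window of the fall item in version 3 of the 30-day survey and version 2 of the 1-year survey, and of the readmission items.
2. Derive days from surgery to survey. The stated exclusions already require this interval.
3. Add it as a prespecified covariate in the 30-day fall and readmission models. If the item asks about the time since surgery, a complementary log-log link with log days as offset is an alternative. The offset assumes a constant hazard, which the 10% and 28% figures do not suggest, so the covariate is the safer default.
4. Use actual person-days in every fall rate, and label the result as the rate over the observed period, since it is not strictly the first-30-day rate.
5. Prespecify a sensitivity analysis limited to surveys completed near day 30, and report the distribution of response days by preoperative fall history.
6. Treat the 275 to 455 day window in the same way.

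The cost is one degree of freedom and a smaller sample in the sensitivity set. On the plan's own rule, 14 variables need 140 events, or 140/0.10 = 1400 patients, still within the roughly 1500 available. No new data are needed.
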